## **PROJECT PROPOSAL**

### ***Background***

The efficacy of social marketing campaigns in facilitating a societal shift in beliefs and attitudes towards low back pain (LBP) is well established. Evidence suggests that campaigns need to be exhaustive and utilise multimedia. The Spinal Pain Model of Care recommends the use of social marketing strategies in WA, specifically mass media campaigns. Development of a single, Government-issued resource which delivers simple, evidence-based messages to the public about active pain management strategies for LBP is the first step in developing a suite of social marketing resources for minimising the burden of spinal pain in WA.

The Spinal Pain Implementation Working Group (SPIWG) has developed a consumer pamphlet which contains evidence-based information about the course of, and self management strategies for, acute and chronic LBP. The pamphlet will be aimed at individuals who seek care for, or information about, LBP in primary care settings (eg pharmacies, GP practices, allied health practices).

The pamphlet has undergone a period of consultation with key professional health bodies and health stakeholders. The pamphlet content is supported by the following professional bodies: Australian Clinical Psychology Association; Australian and New Zealand College of Anaesthetists; Australian Osteopathic Association; Australian Pain Society; Australian Physiotherapy Association; Australian Rheumatology Association (WA); Chiropractors' Association of Australia; Health Consumers' Council; Pharmaceutical Society of Australia (WA); and the Royal Australian College of General Practitioners. Providing the opportunity for the professional bodies of different disciplines to endorse the pamphlet content encourages inter-professional consistency in the delivery of evidence-based information to individuals who seek information about spinal pain. Additionally, messages are targeted towards best-practice *self-management* of spinal pain, where appropriate. Where additional support is required, recommendations to seek evidence-based guidance by health professionals are encouraged.

## ***Aim***

The aim of this project is to undertake an evaluation of the LBP pamphlet within a primary care context. The SPIWG will partner with Curtin University and the Pharmaceutical Society of Australia (WA) (PSA-WA) for the evaluation. The project will determine whether providing the pamphlet to individuals who visit a community pharmacy to purchase pain-relieving medications for LBP is effective in improving beliefs about LBP and minimising fear avoidance behaviours related to LBP, compared to not providing the pamphlet. A secondary aim is to determine whether providing the pamphlet with the pharmacist reiterating the key messages to the consumer is more effective than providing the pamphlet alone.

## ***Design***

A randomized, controlled trial, consisting of 3 study arms (A, B and C), will be undertaken in partnership with 20 community pharmacies in the Perth metropolitan area. A convenience sample of pharmacies will be selected through the PSA-WA. Participating pharmacies will cover major zones of the Perth metropolitan area to represent a range of socioeconomic levels. Ten pharmacies will be involved in both the 'control' (A) and 'pamphlet only' (B) arms while a separate ten pharmacies will be involved in the 'pamphlet with education' (C) arm only. Pharmacies will be allocated to study groups randomly. Each pharmacist who participates in the workshop, will receive training from the evaluation team according to their allocated study arm and remuneration for recruitment.

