## ***Participants***

Pharmacists and/or pharmacy staff will identify individuals who present to the pharmacy to purchase pain-relieving medications for LBP by:

- i) asking customers about the reason for their medication purchase or GP medicine prescription;
- ii) answering questions from customers about medication options for LBP or;
- iii) customers approaching pharmacy staff about the study in response to posters placed in the pharmacy which advertise the study.

Any pharmacy customer aged 18-70 years who is currently experiencing low back pain and has adequate understanding of written and spoken English is eligible to participate. There are no exclusion criteria for this study. Each pharmacy will recruit 12 consecutive customers who meet the inclusion criteria for each study arm. The total sample size will therefore be N=360. Customers who are interested in participating will be asked to complete a consent form and a baseline questionnaire. The completed form and questionnaire will be sent by the pharmacy to Curtin University in a reply paid envelope.

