### ***Outcome measures***

Data will be collected at baseline (T0) and then at 2 weeks (T1), and 8 weeks (T2) after the intervention. Table 1 shows which outcomes measures will be measured at particular time points. Beliefs about back pain will be collected using the Back Pain Beliefs Questionnaire and fear avoidance behaviours will be collected using the Fear Avoidance Beliefs Questionnaire. Pain intensity and disability will be measured using an 11 point numeric rating scale (NRS). Demographic (age, gender, highest level of education) and pain history characteristics (duration of symptoms) will be measured at baseline only while an 11 point NRS for Global Perceived Impression of Usefulness will be used at time points subsequent to baseline to measure the usefulness of the pamphlet.

**Table 1:** Outcome measures assessed by time point.

| Instrument | T0 | T1 | T2 |
|-------------------|-----------|-----------|-----------|
| Demographics      | ✓         |           |           |
| Pain history      | ✓         |           |           |
| BPBQ              | ✓         | ✓         | ✓         |
| FABQ              | ✓         | ✓         | ✓         |
| Pain intensity    | ✓         | ✓         | ✓         |
| GPIU              |           | ✓         | ✓         |
| Disability        | ✓         | ✓         | ✓         |

Participants will be asked to provide informed consent at baseline, including their contact details and date of birth. All data will be collected using a 2 page, teleform paper questionnaire which will be de-identified but linked to person details using a unique study identifier. Data at T0 will be collected onsite at the pharmacy while follow-up questionnaires (T1, T2) will be posted to participants with a reply-paid envelope. All data will be returned to Curtin University for secure storage and analysis. Participants who do not return follow-up questionnaires will be contacted by a project officer and reminded to do so.

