### ***Analysis***

A 3x3 ANOVA with one repeated measure will be used to examine main effects for group (k=3) and time point (k=3), as well as interactions between the factors.

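### Pharmacies are chosen to span zones and socioeconomic levels, but no stratified allocation is specified, which leaves C versus B and C versus A open to chance imbalance

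*Supplement*

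**What the plan says.** The Design section of the project proposal describes a trial that "will be undertaken in partnership with 20 community pharmacies in the Perth metropolitan area". On selection it says "A convenience sample of pharmacies will be selected through the PSA-WA" and "Participating pharmacies will cover major zones of the Perth metropolitan area to represent a range of socioeconomic levels". On arms it says "Ten pharmacies will be involved in both the 'control' (A) and 'pamphlet only' (B) arms while a separate ten pharmacies" serve C only. The method of allocation is one sentence: "Pharmacies will be allocated to study groups randomly". The number of zones or socioeconomic levels is not given, nor is the number of pharmacies expected in each.

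The Participants section adds "Each pharmacy will recruit 12 consecutive customers who meet the inclusion criteria for each study arm", and Interventions confirms that pharmacies 1-10 serve both A and B while pharmacies 11-20 serve C.

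Analysis is a single sentence. It opens "A 3x3 ANOVA with one repeated measure will be used to examine main effects for group (k=3) and time point (k=3" and goes on to the interactions between the two factors. It names no term for pharmacy, zone, socioeconomic level or education. Under Outcome measures, "Demographic (age, gender, highest level of education) and pain history characteristics (duration of symptoms) will be measured at baseline only"; no area-level socioeconomic measure is listed.

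**The concern.** Selection deliberately brings variation between pharmacies into the sample, on a factor that can be known before allocation because it guides selection. Nothing stated then uses that information to balance the two sets of ten.

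Comparisons involving arm C are wholly between pharmacies, ten against ten. If more low-socioeconomic pharmacies fall on one side, customers there may start with different beliefs or respond differently to written or spoken advice. Recruiting 12 customers per pharmacy does not help, because the imbalance lies in which pharmacies are on each side and not in how many customers each supplies. At stake is mainly the secondary aim, whether pharmacist reinforcement adds to the pamphlet (C versus B), and also C versus A.

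**Working it through.** **The plan's own figures.** The proposal states no probability of imbalance. Its only calculation is Appendix 1, which reproduces with two-sided alpha 0.05, 80% power and SD 5.0:
- back beliefs, mean change 1.9: 109.7 by the t-test formula, so 110 per group as stated;
- FABQ-phys, mean change 1.5: 175.4, so 176 as stated.

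Both effects are mean changes, which matters in step 3.

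**Step 1. One illustrative mix.**
- Inputs from Design: 20 pharmacies, fixed sizes 10 and 10.
- Assumption, not in the documents: a two-level factor with K low-socioeconomic pharmacies, and no restriction beyond the 10:10 sizes.

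The number X of low-socioeconomic pharmacies in the A/B set is hypergeometric: P(X = x) = C(K, x) × C(20−K, 10−x) / C(20, 10), with C(20, 10) = 184,756.

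For K = 10, the 7:3 or worse splits in one direction number 14,400 + 2,025 + 100 + 1 = 16,526. Both directions give 33,052, and 33,052 / 184,756 = 17.9%.

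For K = 8, splits of 6:2 or worse give 2 × (13,860 + 1,760 + 66) = 31,372, and 31,372 / 184,756 = 17.0%.

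**Step 2. Range over mixes and thresholds.** Probability of a gap of at least four low-socioeconomic pharmacies between the two sets:

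| K of 20 | 4 | 5 | 6 | 7 | 8 | 9 | 10 | 11 | 12 |
|---|---|---|---|---|---|---|---|---|---|
| Probability | 8.7% | 3.3% | 14.1% | 5.7% | 17.0% | 7.0% | 17.9% | 7.0% | 17.0% |

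The low values at odd K are partly parity: the gap must then be odd, so at least four means at least five. For a gap of at least three they become 30% (K = 5), 35% (K = 7) and 37% (K = 9).

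The threshold matters as much as the mix. With K = 10, 8:2 or worse has probability 2.3%, and 6:4 or worse 65.6%. If socioeconomic level is instead a normally distributed score (simulated), the two sets' means differ by at least 0.5 SD with probability about 26%, and by at least 0.8 SD with probability about 7%.

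**Step 3. What an imbalance does to each planned test.** Let p_C and p_B be the shares of low-socioeconomic pharmacies in each set, d a constant difference in score between low and high pharmacies, and r a difference in their change over time.
- Score difference, C versus B, at every time point: (p_C − p_B) × d. After a 7:3 split this is 0.4 × d. It enters the group main effect and any unadjusted follow-up comparison.
- Difference in change from T0: (p_C − p_B) × (d − d) = 0. A constant d cancels from the group-by-time interaction.
- If change itself differs by r, the difference in change shifts by (p_C − p_B) × r. Only then is the interaction exposed. The documents give neither d nor r.
- A versus B: the same ten pharmacies supply both arms, so the shares are identical and the shift is zero.

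**Step 4. After stratifying.** With two strata of ten allocated 5:5, the gap is zero. With odd-sized strata the sets differ by at most one pharmacy per stratum.

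**The case against.** Four objections deserve a fair hearing.

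*The method is unspecified, not unrestricted.* A reader might infer that simple randomisation is planned. The text says only that allocation is random, with fixed set sizes; restriction is neither described nor excluded. This stands: the defect is silence about the method. Allocation method does, however, belong in a design section. A model term could be left to a fuller analysis plan, and none is shown, so the main weight of the point rests on allocation.

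*The effect cannot be sized in points.* A reader might assume a 2-point score difference (range 1-3), obtain 0.4 × 2 = 0.8 points (0.4-1.2) from a 7:3 split, and call it a bias of 42% (21-63%) of the 1.9 points in Appendix 1. The documents do not support that. The 2 points are not in them, and the ratio sets a difference in score level against a mean change. With T0 measured before the pamphlet is given, a constant level difference cancels from the interaction, which is the test of differential change.

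*Chance imbalance is variance, not systematic bias.* This is right over repeated allocations. Stratifying removes that part of the variance, and the trial is allocated only once.

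*Education is recorded and could serve for adjustment.* It could, as an individual-level proxy, but the Analysis section does not use it.

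**Conclusion.** The point holds as a low-cost improvement to the comparisons involving arm C. The proposal selects pharmacies for socioeconomic spread, specifies no restriction in allocating them, and names no balancing factor in the analysis.

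The 17.9% is an illustration. It rests on a two-level factor, exactly 10 low-socioeconomic pharmacies of 20, a 7:3 threshold, and no restriction beyond the 10:10 sizes. A reader might take about 18% as a property of this plan; the documents give no mix that would support it. The fair statement is about 3% to 18% for a gap of at least four pharmacies over mixes of 4 to 12, with much lower or higher values under other thresholds.

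Nor should a reader infer that the pamphlet-versus-control comparison of B with A is at risk from this source. For C versus B and C versus A, the group main effect and unadjusted follow-up comparisons are exposed to a constant score difference. The interaction is exposed only if response differs by socioeconomic level, and the size of that cannot be derived from the documents.

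**What to change.** In Design, extend the allocation sentence along these lines: once all 20 pharmacies are enrolled and before any is allocated, they will be classified into two or three zone/socioeconomic strata; within each stratum, pharmacies will be allocated at random in equal numbers (to within one where the stratum is odd-sized) to A/B or to C, keeping ten in each set. In Analysis, include the stratum as a term in the C versus B and C versus A comparisons.

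The costs are modest. The strata must be defined, since zone and socioeconomic level are not the same thing and the proposal defines neither. Every pharmacy must be enrolled before allocation. In an analysis at the pharmacy level, 20 pharmacies in two sets leave 20 − 2 = 18 degrees of freedom; two or three strata use one or two of these, leaving 17 or 16. Full pairing would use nine, leaving 9, so a few strata are preferable. No extra pharmacies, customers or questionnaires are needed.

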## ***Participants***

Pharmacists and/or pharmacy staff will identify individuals who present to the pharmacy to purchase pain-relieving medications for LBP by:

- i) asking customers about the reason for their medication purchase or GP medicine prescription;
- ii) answering questions from customers about medication options for LBP or;
- iii) customers approaching pharmacy staff about the study in response to posters placed in the pharmacy which advertise the study.

Any pharmacy customer aged 18-70 years who is currently experiencing low back pain and has adequate understanding of written and spoken English is eligible to participate. There are no exclusion criteria for this study. Each pharmacy will recruit 12 consecutive customers who meet the inclusion criteria for each study arm. The total sample size will therefore be N=360. Customers who are interested in participating will be asked to complete a consent form and a baseline questionnaire. The completed form and questionnaire will be sent by the pharmacy to Curtin University in a reply paid envelope.

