### ***Interventions***

Interventions will be phased in the following sequence:

**A) Control (pharmacies 1-10):** pharmacists will be asked to invite the first 12 customers who meet the inclusion criteria to participate in the study as a control (N=120). In the control arm, customers will not receive any information about self-management for LBP (i.e.; will receive ‘usual care’ only).

**B) Pamphlet only (pharmacies 1-10):** pharmacists will be asked to invite the next 12 customers, that is the next 12 customers after the control participants have been recruited, who meet the inclusion criteria, to participate in the study (N=120). In this arm, participants will receive a pamphlet from the pharmacist without any further information about self management, other than usual instructions from the pharmacist relating to medication intake, dosage and side-effects. Baseline data will be collected *prior to* the pamphlet being provided.

**C) Pamphlet with education (pharmacies 11-20):** pharmacists will be asked to invite the first 12 customers who meet the inclusion criteria to participate in the study (N=120). In this arm, participants will receive a pamphlet from the pharmacist *and* the pharmacist will review the content of the pamphlet with the participant. Information provided by pharmacists will be standardised. Baseline data will be collected *prior to* the pamphlet and further information being provided. The role of the pharmacist will be to reinforce the key messages contained in the pamphlet

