### ***Feasibility***

Using a partnership arrangement between Health Networks, Curtin University, Musculoskeletal Health Network and the Pharmaceutical Society of Australia, completion of data collection is feasible within 6 months with a budget of \$14,300. It is envisaged that recruitment of participants from 20 pharmacies for each arm of the study will be possible within 4 week blocks; ie 12 participants per pharmacy per 4 week block (3 customers per week). Providing a modest remuneration to each pharmacy will also assist with recruitment.

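### Arm B runs inside every control's 8-week follow-up at the same pharmacies, and nothing bars a returning control from joining B, so the control arm can be contaminated before T2

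*Supplement*

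**What the plan says.** All references are to the project proposal in the Supplement.

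- **Design:** "Ten pharmacies will be involved in both the 'control' (A) and 'pamphlet only' (B) arms". Arm C uses ten other pharmacies.
- **Interventions:** arm A takes the first 12 eligible customers at each of the ten pharmacies. Arm B then takes "the next 12 customers after the control participants have been recruited". The trigger is the end of control recruitment, not the end of control follow-up, and no gap is stated. For controls, "customers will not receive any information about self-management for LBP".
- **Feasibility:** the planned pace is "12 participants per pharmacy per 4 week block (3 customers per week", with data collection completed in 6 months.
- **Outcome measures:** "Data will be collected at baseline (T0) and then at 2 weeks (T1), and 8 weeks (T2) after the intervention".
- **Participants:** the population is "Any pharmacy customer aged 18-70 years who is currently experiencing low back pain", with adequate English. Recruitment is consecutive, and "There are no exclusion criteria for this study".
- **Analysis:** a 3x3 ANOVA with group as the between-person factor and time as the repeated factor.

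No section says what to do if a control returns during the B block, or how a person enrolled twice would be analysed.

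**The concern.** The first aim is to compare giving the pamphlet with not giving it. That needs controls to stay without the pamphlet until their last measurement. Here the pharmacy that enrolled a control changes to handing out pamphlets before that control's T2.

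The people recruited are buying medicine or filling prescriptions for back pain, so some may well return to the same pharmacy within weeks. Applied literally, consecutive recruitment with no exclusions means that such a person should be invited into B. Completed consent forms and baseline questionnaires go to the university, and no pharmacy record of earlier participants is described. Pharmacies are paid per recruit, and nothing limits payment to new people.

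Three things would follow from a re-enrolment:

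- The control's T2 score is measured after receiving the pamphlet. This pulls both A-B and A-C towards no difference.
- One person sits in two levels of the between-group factor, so the groups are no longer independent.
- That person enters B having already answered the questionnaires at least once.

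**Working it through.** **1. Calendar.** Put the start of A at week 0. With 4-week blocks and no gap, A recruits in weeks 0 to 4 and B in weeks 4 to 8. A control enrolled at week t (0 to 4) has T1 at t+2 and T2 at t+8.

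- Overlap of B with follow-up to T2 = min(t+8, 8) − max(t, 4) = 8 − 4 = 4 weeks, for every t from 0 to 4.
- Overlap of B with follow-up to T1 = max(0, t+2−4) = max(0, t−2). This is 0 for controls enrolled in weeks 0 to 2 and rises to 2 weeks for those enrolled at week 4.

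**2. Eligibility of a returning control.** The stated conditions are age 18-70, current low back pain and adequate English. A control met all of them at entry and, if still in pain, meets them again in weeks 4 to 8.

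**3. The plan's own sample size (Appendix 1).** Inputs for the BBQ: difference 1.9, SD 5.0, power 80%, alpha 0.05 (two-sided assumed; the plan does not say).

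n = 2 × (1.960 + 0.842)² × 5.0² / 1.9² = 108.7, so 109 per group. The plan states 110. Adding the usual small-sample term 1.96²/4 = 0.96 gives 109.7, so 110. For FABQ-phys with 1.5 points the same steps give 175 without that term, against 176 stated. Both figures are reproduced.

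**4. Illustrative dilution.** Let c be the share of controls who receive the pamphlet before T2, and assume that each gains the full effect by then. The A-B difference becomes δ(1−c). The standard error at 120 per arm is 5 × √(2/120) = 0.6455, and power = Φ(δ(1−c)/0.6455 − 1.96). At c = 10%: 1.71/0.6455 = 2.649; 2.649 − 1.96 = 0.689; Φ = 0.755.

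| Controls exposed (c) | Former controls in B, of 120 | BBQ difference | BBQ power | BBQ n per group for 80% | FABQ-phys power |
|---|---|---|---|---|---|
| 0% | 0 | 1.90 | 83.7% | 109 | 64.2% |
| 5% | 6 | 1.805 | 79.9% | 121 | 59.8% |
| 10% | 12 | 1.71 | 75.5% | 135 | 55.2% |
| 20% | 24 | 1.52 | 65.4% | 170 | 46.0% |

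The second column follows because enrolment in B is the only documented way for a control to get a pamphlet at these pharmacies, so each exposed control takes one of the 120 B places. The values of c are assumptions; the documents give none. The table covers dilution only. It leaves out the lost independence, clustering by pharmacy, and dropout.

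**The case against.** The strongest reply is that the plan already points away from re-enrolment. Controls are to get no self-management information, so knowingly giving one the pamphlet would conflict with the control condition. The next 12 customers are most naturally read as different people, and N=360 is the plain sum of three arms of 120. Consent collects date of birth and contact details linked to a study identifier, so duplicates could be found. Item B1 at T1 and T2 has a not-applicable option, so control exposure could be seen. This stands as far as intent and detectability go. It does not close the gap: no sentence bars an earlier participant, the stated eligibility rule admits one, and no check is planned.

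It is also fair to say that the higher rates in the table are demanding. At 20%, 24 of the 120 B participants would have to be former controls who agreed to a second consent and baseline within weeks. At 5%, power is still about the planned 80%. The full-effect assumption is also generous for someone exposed shortly before T2.

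Two stronger readings are tempting. A reader might infer that the control arm **is** contaminated. The documents show only that it can be. A reader might also count all the time from the opening of B to each control's T2, which gives 4 to 8 weeks with a mean of 6. That treats B as never closing. The plan sets 12 B participants per pharmacy in a 4-week block, and nothing says that pamphlets are handed out afterwards. The overlap is 4 weeks, and longer only if B recruitment runs late.

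**Conclusion.** The point holds as a risk written into the design. The planned B block lies entirely within every control's follow-up, and the eligibility rule as written lets a control into B. Any bias would be towards no difference for A-B and A-C, mainly at T2. T1 is largely protected, but controls enrolled in the second half of the A block have up to 2 weeks of overlap before it.

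The size is unknown. On the illustrative figures, the BBQ margin from 110 to 120 per group is used up at about 5% exposure, before any dropout.

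The conclusion assumes that B starts without a gap and that recruitment keeps to the 4-week pace. The consent form and the items of the baseline questionnaire were not in the text available for review, so a question there about earlier participation cannot be ruled out. It would not alter the stated rule that there are no exclusions. The sample size figures in Appendix 1 are not in error on this account.

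**What to change.** 1. Replace the statement that there are no exclusions with one criterion: already enrolled in this study, in any arm.
2. Keep an enrolment list at each of the ten A/B pharmacies, and have staff check it before inviting anyone.
3. State that an arm A participant is not given the study pamphlet before that person's T2 due date. Use the due date, not return of the form: T2 is posted and goes back to the university, so pharmacy staff would not know whether it had been returned.
4. At the university, check for duplicates across all 20 pharmacies using the date of birth and contact details already collected. State in advance how any duplicate will be analysed, and report control responses to item B1 as a check on exposure.

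The cost is a few protocol sentences, a list that must be kept securely at ten sites, and a simple data check. A few returning customers will be turned away, which may slow B slightly.

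Opening B only after the last control T2 would remove the overlap, but it is not needed if the steps above are taken. It would take 4 + 8 + 4 + 8 = 24 weeks, against about 26 in the planned 6 months, and would move A and B further apart in calendar time.
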